### Follow-up

After randomization, subjects will have follow-up after 3, 6 and 12 months, mainly in the outpatient clinic according to Figure 2.
(1)The survival status will be confirmed and rehospitalization and occurrence of MACE events will be requested by telephone(2)Holter electrocardiogram (>24 h), transthoracic heart color ultrasound, blood test of blood potassium and kidney function will be performed in the outpatient clinic(3)Adverse event assessment, the main adverse reactions assessed will be: hypotension, high blood potassium, impairment of renal function, as determined in the outpatient clinic(4)Medication consumption in the past will be requested by telephone;(5)Drug bottles will be collected, and the subject reminded of the importance of study medication compliance by the outpatient clinic.

**Figure 2 F2:**
[figure not shown]
Schedule of enrollment, interventions and assessments for the trial.

### Sample size

The determination of the sample size in this study will be driven by the need of the above strategy to detect sacubitril/valsartan over conventional drugs.

The recurrence rate of atrial fibrillation after 12 months in patients with persistent AF is approximately 42% (15), and we expect a 20% decrease in the incidence of primary endpoint events taking ARNI after catheter ablation in patients with persistent AF. Under the assumption based on the exponential distribution, the risk ratio is 0.46.

Based on the above assumptions, the expected enrollment time is 24 months, without considering the mid-term analysis, and the minimum follow-up time is 12 months. Assuming a 20% missing visit in each of the control and trial groups, the study requires 450 participants (225 trial group, 225 control group) to obtain 90% difference at a significance level of *a* = 0.05 (unilateral). The sample size is calculated by PASS15.0 software. The interim analyses is set up by the O'Brien-Fleming method to control the overall Type I error below 0.05. The final sample size will be 462 cases (231 trial group, 231 control group).

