Interim analyses of key safety and endpoint metrics will be conducted periodically during the course of the trial. Two interim analyses will be conducted when 33% and 67% of the total number of planned primary endpoint events have been reached. Interim analyses will be performed using the O'Brien-Fleming method to maintain an overall significance level of 0.05. The significance level alpha for the two interim and final analyses is 0.0015, 0.0172, and 0.0313, respectively. The independent Data Monitoring Committee will review the safety and efficacy of the trial based on interim analysis results.

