### Trial status

The recruitment date is from 2022/08/30 To 2025/08/30. The trial is currently recruiting patients.

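### The sample size of 450 (462) does not follow from its stated inputs, which need about half as many patients or fewer; 462 gives about 99% power for the stated effect, not 90%

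*Protocol article*

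**What the plan says.** All the inputs stand in the Sample size section of the protocol article.

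- Control rate: "The recurrence rate of atrial fibrillation after 12 months in patients with persistent AF is approximately 42"%.
- Effect: "we expect a 20% decrease in the incidence of primary endpoint events", without saying whether the 20% is absolute or relative.
- Ratio: "Under the assumption based on the exponential distribution, the risk ratio is 0.46".
- Timing: 24 months of enrolment and at least 12 months of follow-up.
- Loss: 20% missing visits in each arm, with no time unit.
- Error rates: the 90% figure is worded "to obtain 90% difference at a significance level of" and can only sensibly mean power; alpha is "0.05 (unilateral").
- Result: "the study requires 450 participants (225 trial group, 225 control group) to obtain 90% difference at a significance level of" 0.05, then 231 per arm, 462 in total, once the O'Brien-Fleming interims are allowed for.

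Three other sections bear on this. Primary outcome and Follow-up set the endpoint within 12 months, with the last visit at month 12. Statistical and analytical plans names the log-rank test and says "Two interim analyses will be conducted when 33% and 67% of the total number of planned primary endpoint events have been reached". Trial status says "The recruitment date is from 2022/08/30 To 2025/08/30", which is 36 months, and Study design gives the same period.

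**The concern.** A hazard ratio of 0.46 is a large effect. At one-sided 0.05 and 90% power it needs only some 60 events, and with recurrence of 42% and 22% a few hundred patients produce those easily. A requirement of 225 per arm therefore looks about twice too large, or more.

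Two things are at stake. First, the power statement tells readers what the trial can detect. If 90% is wrong for 0.46, a reader of a null result will misjudge which effects have been excluded. Second, the interim looks are fractions of a planned event total. Someone deriving that total from the hazard ratio and power gets a very different number from someone deriving it from 462 patients.

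**Working it through.** **Step 1: reproduce the ratio.** Under exponential event times, HR = ln(1 − p_trial)/ln(1 − p_control).

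- Absolute drop, 42% to 22%: ln(0.78)/ln(0.58) = 0.2485/0.5447 = 0.456, which rounds to the printed 0.46.
- Relative drop, 42% to 33.6%: ln(0.664)/ln(0.58) = 0.752.

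Only the absolute reading gives 0.46, so the effect is settled as 42% to 22%.

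**Step 2: events needed.** One-sided 0.05 and 90% power give (1.645 + 1.282)² ≈ 8.56.

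- Schoenfeld, 4 × 8.56/(ln HR)²: 55.6 for HR 0.456; 56.8 for 0.46.
- Freedman, 8.56 × [(1 + HR)/(1 − HR)]²: 61.4 for HR 0.456; 62.6 for 0.46.

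**Step 3: patients needed.** Divide events by the mean event probability, then by 0.8 for loss.

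For fixed 12-month follow-up the mean event probability is (0.42 + 0.22)/2 = 0.32. For the stated accrual model, each arm has 1 − (e^(−12λ) − e^(−36λ))/(24λ). With control λ = 0.5447/12 per month this is 0.647 for control and 0.385 for trial, mean 0.516.

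| Follow-up model | Low: Schoenfeld, HR 0.456 | High: Freedman, HR 0.46 |
|---|---|---|
| Fixed 12 months | 55.6/0.32/0.8 = 217 | 62.6/0.321/0.8 = 244 |
| 24-month accrual + 12-month minimum | 55.6/0.516/0.8 = 135 | 62.6/0.517/0.8 = 151 |

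These are totals for both arms. Two-sided 0.05 with fixed 12 months gives about 266 to 299. A comparison of two proportions (42% against 22%, one-sided) gives 230, or 256 with continuity correction. None comes near 450.

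**Step 4: power of 462.** With 20% lost and contributing nothing, events = 462 × 0.8 × 0.32 = 118.3. Power = Φ(√(118.3/4) × 0.785 − 1.645) = Φ(2.62) = 99.6% one-sided; allowing for the interims it is 99.5%. Two-sided it is about 99%.

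**Step 5: what 462 detects with 90% power.** Solve √(D/4) × |ln HR| = 2.927, with D = 462 × 0.8 × mean event probability at that HR. One-sided, HR = 0.597, trial-arm recurrence 1 − 0.58^0.597 = 27.8%, about 129 events. Two-sided, HR = 0.562, recurrence 26.4%, about 126 events.

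**Step 6: event totals for the looks.**

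| Basis | Total | 33% | 67% |
|---|---|---|---|
| HR 0.46 and 90% power | 57 | 19 | 38 |
| 462 patients, lost patients contribute nothing | 118 | 39 | 79 |
| 462 patients, 20% loss spread over the year | 134 | 44 | 90 |

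The last row uses exponential loss with 20% gone by month 12. Event probabilities are then 0.380 and about 0.20, mean 0.29, and 462 × 0.29 ≈ 134.

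**Step 7: can any reading reach 450?** One comes close. If the 20% is entered as loss per month with 24 + 12 months, the mean event probability falls to 0.126 and 57/0.126 ≈ 450. The article states no monthly rate, and 0.8^12 = 0.069, so about 7% of patients would still be under observation at month 12.

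**The case against.** The strongest reply is that the loss has no time unit and the software input is not shown, so 450 may have come from a definite calculation, such as the monthly-loss reading. That stands as a possible cause, but it does not rescue the figure: such a rate is not stated, and it is incompatible with a trial whose endpoint is read at 12 months. A reader might also infer that a total near 225 was taken as per arm. That too is possible, but the document cannot show which slip occurred, if either.

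A second reply is that no single corrected number is the answer. This stands. The 217 to 244 range uses the 12-month endpoint window, while the accrual model in the Sample size section gives 135 to 151. The conclusion does not depend on the choice, since both are far below 450.

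A third is that a journal article may leave the absolute event target to the full protocol or a monitoring charter. This stands as well: the missing number is not in itself an error, and one cannot infer from it that the looks cannot be placed. What remains is that the published inputs point to totals differing by more than a factor of two.

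A fourth is that the enrolment mismatch is minor. August 2022 to August 2025 equals 24 months of enrolment plus 12 of follow-up, so the recruitment wording may be loose. The sections still disagree as written, though longer accrual would not bring the requirement up to 450.

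Finally, a reader who takes the 20% as relative would compute about 52% power at 462 and call the trial underpowered. The printed 0.46 rules that reading out.

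**Conclusion.** The point holds as a correction to the stated design basis; it should be fixed. The stated inputs need about 56 to 63 events, hence about 217 to 244 patients with 12-month follow-up or 135 to 151 under the stated accrual model, against 450 stated. Power at 462 for a hazard ratio of 0.46 is about 99%, and 90% power belongs to a hazard ratio of about 0.60 one-sided or 0.56 two-sided.

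This rests on exponential event times, 1:1 allocation, a log-rank comparison and 20% loss over the whole of follow-up. The documents do not support the stronger conclusion that the primary test is compromised: the discrepancy is in the safe direction for power, and it leaves the endpoint and the planned test as they are.

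**What to change.** Keep 462 and rewrite the Sample size paragraph after checking the inputs entered in the software:

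- State the decrease as absolute, 42% to 22%, and call the 90% figure power.
- Give the time unit of the 20% loss.
- Use one follow-up model that matches the 12-month endpoint.
- Reconcile the 24-month enrolment with the August 2022 to August 2025 recruitment dates.
- Replace the 90% statement with the true power for 0.46 (about 99%) or with the effect that 462 detects at 90% power. If the second is chosen, present it as what the sample size can detect, not as a new expected effect; the target effect remains the sponsor's decision.
- Derive the planned event total for the 33% and 67% looks from the corrected calculation, state the loss model behind it, and fix it before the first look. This matters more in an open-label trial, where the total should not be chosen once data have accrued.

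The cost is one restated paragraph and one fixed number for the data monitoring committee. No additional patients are needed.

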### Statistical and analytical plans

The statistical analysis will be along with the intention-to-treat (ITT) principles. The ITT population will include patients who meet the criteria, are randomized, and take at least one dose of drugs after being enrolled. For statistical description, continuous variables are described by using mean and standard deviation if they satisfy a normal distribution, skewed distributions are described by medians and quartiles, while categorical variables will be presented as frequency or percentage in each category. For the baselines, the t-test is used to compare the differences for quantitative variable if the data meets the normality test, otherwise, the data will be transformed or rank sum test. Categorical variables such as disease history and smoking history can be tested using chi-square test or rank sum test. For outcomes such as 239sinus rhythm maintenance rate, all-cause death, re-hospitalization rate for cardiovascular causes and MACE, Kaplan-Meier curves will be used to characterize how the probability of an endpoint event changes with survival time, and comparisons between survival curves will be carried out using log-rank tests. We used cox proportional hazards models to estimate hazard ratios and 95% confidence intervals. Cardiac structural function indicators will be described by mean value (±SD) or median and quartiles, and the sphericity of the covariance array will be tested by the Mauchly method. If the data satisfies the sphericity of the covariance array, the analysis of variance with repeated measures data will be used for group comparisons of each indicator. If it is not satisfied, the Greenhouse-Geisser method will be used for comparison of differences. Missing observations will be accounted for using the predictive mean matching (PMM) method. If the missing data is numerical, it will be filled by predictive mean matching; meanwhile if the missing data is non-numerical, logistic regression and discriminant functions will be used to fill it. The *p*-value threshold is 0.05(*p* < 0.05), and when it is below this threshold, indicating that the difference is statistical significant. SPSS statistical software (SPSS Inc, Chicago, IL, USA, version 23) will be used to analyse data.

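### The trial is sized and monitored at one-sided 0.05, but the analysis section uses 95% confidence intervals and a p < 0.05 rule with no side, so the criterion for success is not fixed

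*Protocol article*

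**What the plan says.** Three places in the protocol article bear on the level of the primary test.

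- **Sample size.** The calculation is made "at a significance level of *a* = 0.05 (unilateral"). Its other inputs are a 12-month recurrence of 42% in controls, an expected decrease of 20%, a ratio of 0.46, 90% power (worded as "to obtain 90% difference") and 20% loss per arm. The result is 450 patients, raised to 462 for the O'Brien-Fleming interim analyses.
- **Statistical and analytical plans, main paragraph.** Time-to-event outcomes, including sinus rhythm maintenance, are compared by log-rank test, and "We used cox proportional hazards models to estimate hazard ratios and 95% confidence intervals". A p-value below 0.05 is called significant. No side is given.
- **Statistical and analytical plans, interim analyses.** Looks are planned at 33% and 67% of the planned primary events, using O'Brien-Fleming "to maintain an overall significance level of 0.05". The levels for the two interim analyses and the final one are 0.0015, 0.0172 and 0.0313, again with no side.

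Nowhere is the 95% interval tied to the test level.

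**The concern.** A 95% interval excludes 1 in favour of the drug only when z reaches 1.960, which is one-sided 0.025. A one-sided 0.05 test needs less. If the one-sided level governs the primary test, there is a range of results that the test calls a success and the reported interval does not.

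One-sided 0.05 also allows a 5% chance of wrongly claiming benefit, twice the 2.5% that the interval implies. The protocol gives no reason for that choice. The same final data could therefore count as a success under one section and a failure under another.

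**Working it through.** **1. Planned effect.** Under exponential event times, 42% against 22% recurrence gives ln(0.78)/ln(0.58) = 0.456, which reproduces the stated 0.46. The 20% decrease is thus an absolute one.

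**2. Which level lies behind the interim figures.** For three looks at 1/3, 2/3 and 1 of the events, the classical O'Brien-Fleming boundary is z_k = C/√t_k.

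| Overall level | C | Error spent at each look | Nominal p at each look |
|---|---|---|---|
| one-sided 0.05 | 1.710 | 0.00153, 0.01721, 0.03126 | one-sided 0.0015, 0.0181, 0.0437 |
| one-sided 0.025 | 2.004 | 0.0003, 0.0069, 0.0178 | two-sided 0.0005, 0.0141, 0.0451 |

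The protocol's 0.0015, 0.0172 and 0.0313 match the error spent in the first row to four decimals, and they sum to 0.0500. They are increments, not nominal p-value thresholds.

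**3. The step from 450 to 462.** At 90% power the inflation factor is 1.0249 for one-sided 0.05, and 450 × 1.0249 = 461.2, or 462 in equal arms. For one-sided 0.025 it is 1.0161, giving 457.2. The interim adjustment was therefore also made at one-sided 0.05.

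**4. Number of events (assumption).** The protocol gives no event count. Two values bracket it:

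- Fixed 12-month follow-up, average event probability (0.42 + 0.22)/2 = 0.32: 462 × 0.8 × 0.32 = 118.3.
- 24 months of uniform accrual with a 12-month minimum, average probability 0.516: 462 × 0.8 × 0.516 = about 191.

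**5. Result just at the final threshold.** SE(log HR) = 2/√events; critical HR = exp(−z × SE); upper 95% limit = exp((1.960 − z) × SE).

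| Reading of the final level | z | 118 events: HR (95% CI) | 191 events: HR (upper limit) |
|---|---|---|---|
| 0.0313 as one-sided nominal level | 1.862 | 0.710 (0.495–1.018) | 0.76 (1.014) |
| One-sided boundary implied by the increments | 1.710 | 0.730 (0.509–1.047) | 0.78 (1.037) |
| Two-sided 0.05, no looks | 1.960 | 0.697 (0.486–1.000) | 0.75 (1.000) |
| 0.0313 as two-sided nominal level | 2.153 | 0.673 (0.469–0.965) | 0.73 (0.972) |

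Both one-sided readings leave the interval across 1; the two-sided readings do not. At 118 events the range of conflict is HR 0.697 to 0.710 on the first reading and 0.697 to 0.730 on the second. It arises only at the final analysis, because the one-sided interim boundaries (z = 2.961 and 2.094) already exceed 1.960.

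**6. Power after a change to two-sided 0.05.** At HR 0.456 and 118.3 events, three-look power is 99.5% at one-sided 0.05 and 98.9% at two-sided 0.05. However, the stated 450 does not follow from the printed inputs: one-sided variants give totals of about 109 to 268. If 450 gives exactly 90% one-sided power through inputs not shown, two-sided power at 450 is Φ(1.645 + 1.282 − 1.960) = about 83%, and 90% would need 450 × [(1.960 + 1.282)/(1.645 + 1.282)]² = about 552.

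**The case against.** The one-sided choice is stated openly, and a 95% interval reported beside a prespecified one-sided test is an estimate, not a decision rule. The p < 0.05 threshold is a general one that also covers baseline and secondary comparisons, while the interim paragraph governs the primary endpoint. The side of the analysis test may be given in an analysis plan not shown.

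Much of this is fair. A reader might infer that the protocol definitely permits a win with an interval that includes 1, for instance at HR 0.73. The documents do not support that unconditionally. The analysis section never calls the test one-sided, and HR 0.73 has a one-sided p of about 0.044, which fails the printed final level of 0.0313 if that is taken literally. The boundary z = 1.710 is reconstructed and not printed. Taken literally as one-sided nominal levels, the three figures give an overall error of about 3.9%, not 5%.

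The conflict itself remains. The literal one-sided reading still gives an upper limit above 1, and the two-sided reading contradicts the level behind both the sample size and the interim figures. This is not a detail left to a later plan: the protocol itself fixes the level, the interval and the boundaries, and they do not agree.

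**Conclusion.** The point holds as an inconsistency in side and level that leaves the primary criterion open. That sizing and monitoring rest on one-sided 0.05 follows from the stated wording, the match of the three increments and the step to 462; none of this depends on an assumed event count. The size of the conflict does: critical hazard ratios of 0.710 to 0.730 at about 118 events, or about 0.76 to 0.78 at about 191, all with upper 95% limits above 1, and only if the primary test is one-sided.

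A reader might also infer that moving to two-sided 0.05 is certain to be free because 462 looks ample. The printed inputs point that way, but since 450 cannot be reproduced from them, it is not established.

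**What to change.** State one side and one level in the Sample size section and in both parts of Statistical and analytical plans, before any unblinded look.

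- **Preferred:** two-sided 0.05 (one-sided 0.025), with nominal two-sided O'Brien-Fleming p-values of 0.0005, 0.0141 and 0.0451, keeping the 95% interval. Say that these are nominal p-values and that the present figures are error increments; otherwise the move from 0.0313 to 0.0451 would look like a relaxation when the final threshold in fact tightens from z = 1.710 to 2.004.
- **Alternative:** keep one-sided 0.05, say so in the analysis section, print the nominal one-sided boundaries 0.0015, 0.0181 and 0.0437, and report the matching 90% (or look-adjusted) interval.

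The preferred route costs a stricter threshold (critical HR about 0.69 at 118 events, 95% CI 0.482 to 0.992) and a restated power: about 98.9% on the printed inputs, or about 83% if 450 was only just enough for 90% one-sided. In that second case the lower power should be reported; the point does not call for enrolling more patients.

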### Data collection and management

Blank case report forms (CRFs) that has been ethically approved will be used to record data for all participants. Each enrolled patient corresponds to a complete CRF, and unrecorded data will be labeled and justified. The CRFs will be entered into the scientific research platform of the First Affiliated Hospital of Shantou University Medical School in a double-entry manner by researchers. Researchers are responsible for the completeness and accuracy of the records. A CRF will include:
(1)Medical history or medical examination data(2)Informed consent of the subjects and the randomization number of this trial(3)Time of each follow-up visit and signed notes(4)Reported adverse events and their resolution or absence, including documentation such as hospitalization records, discharge summary, ECG, etc(5)Record of the medication use of the test subjects during the trial

### Statistical and analytical plans

The statistical analysis will be along with the intention-to-treat (ITT) principles. The ITT population will include patients who meet the criteria, are randomized, and take at least one dose of drugs after being enrolled. For statistical description, continuous variables are described by using mean and standard deviation if they satisfy a normal distribution, skewed distributions are described by medians and quartiles, while categorical variables will be presented as frequency or percentage in each category. For the baselines, the t-test is used to compare the differences for quantitative variable if the data meets the normality test, otherwise, the data will be transformed or rank sum test. Categorical variables such as disease history and smoking history can be tested using chi-square test or rank sum test. For outcomes such as 239sinus rhythm maintenance rate, all-cause death, re-hospitalization rate for cardiovascular causes and MACE, Kaplan-Meier curves will be used to characterize how the probability of an endpoint event changes with survival time, and comparisons between survival curves will be carried out using log-rank tests. We used cox proportional hazards models to estimate hazard ratios and 95% confidence intervals. Cardiac structural function indicators will be described by mean value (±SD) or median and quartiles, and the sphericity of the covariance array will be tested by the Mauchly method. If the data satisfies the sphericity of the covariance array, the analysis of variance with repeated measures data will be used for group comparisons of each indicator. If it is not satisfied, the Greenhouse-Geisser method will be used for comparison of differences. Missing observations will be accounted for using the predictive mean matching (PMM) method. If the missing data is numerical, it will be filled by predictive mean matching; meanwhile if the missing data is non-numerical, logistic regression and discriminant functions will be used to fill it. The *p*-value threshold is 0.05(*p* < 0.05), and when it is below this threshold, indicating that the difference is statistical significant. SPSS statistical software (SPSS Inc, Chicago, IL, USA, version 23) will be used to analyse data.

Interim analyses of key safety and endpoint metrics will be conducted periodically during the course of the trial. Two interim analyses will be conducted when 33% and 67% of the total number of planned primary endpoint events have been reached. Interim analyses will be performed using the O'Brien-Fleming method to maintain an overall significance level of 0.05. The significance level alpha for the two interim and final analyses is 0.0015, 0.0172, and 0.0313, respectively. The independent Data Monitoring Committee will review the safety and efficacy of the trial based on interim analysis results.

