**Methods:**

This is a multi-center, randomized, controlled, open-label, superiority clinical trial involving 462 patients without reduced ejection fraction heart failure after catheter ablation of persistent atrial fibrillation. Patients will be randomized to (1) receive the standard treatment strategy plus sacubitril/valsartan titration, or (2) receive the standard treatment strategy without taking sacubitril/valsartan. The primary outcome will be sinus rhythm maintenance rate over 12 months, monitored by random electrocardiogram and 24-h Holter electrocardiogram.

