### Interventions

For all patients enrolled, if they are taking ACEI drugs, they will be given the trial drug starting 36 h after discontinuation of ACEI drugs. The control group will be given conventional perioperative medications according to guidelines of atrial fibrillation, and the trial group will receive conventional perioperative drug therapy plus sacubitril/valsartan (Beijing Novartis Pharmaceutical Company, J20171054). The test drug will be titrated according to Figure 1. The target maintenance dose is 100 mg twice per day. Based on the patient tolerance, drug dosage will be doubled every 2 weeks. If the patient cannot tolerate the maximum dose, the dose will be reduced to the maximum dose tolerated by the patient. In order to increase patient medication compliance, patients will be reminded to take drugs on time by WeChat. When patients change the dose, patients will be required to bring the packaging box of the drugs. Blood pressure, blood potassium and renal function examination will be performed at each follow-up period. If hypotension or symptomatic hypotension occurs, the dose will be adjusted.

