### Conventional perioperative medications

Patients will be treated by standard treatment according to current guidelines (11). They will be on an uninterrupted anticoagulation regimen during the perioperative period. Uninterrupted oral anticoagulation will be taken based on stroke/thromboembolic risk during the perioperative period of AF catheter ablation for enrolling patients (9). Patients can use antiarrhythmic drugs such as Class III drugs (amiodarone) when appropriate based on the judgment of the responsible physician during the 3-month blanking period.

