### Blinding

This trial is designed as an open label. Trial participants and care givers will not be blinded to the group assignment while the investigator or other relevant personnel will not be made aware of the information about the treatment subgroup to which they are assigned until the order of enrollment/randomization of the subjects has been confirmed. Data analysts and outcome evaluator will remain blinded to minimize trial bias.

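### The population called ITT is a modified ITT set: it requires eligibility and at least one dose of undefined drugs, and no analysis of all randomised patients is stated

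*Protocol article*

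**What the plan says.** The section on statistical and analytical plans opens with the principle: "The statistical analysis will be along with the intention-to-treat (ITT) principles". Its next sentence defines the population: "The ITT population will include patients who meet the criteria, are randomized, and take at least one dose of drugs after being enrolled". The article names no other efficacy population and does not say which drugs count towards the dose condition.

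Four other places bear on how that definition would work:

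- **Control treatment.** The abstract says controls "receive the standard treatment strategy without taking sacubitril/valsartan". The Interventions section adds: "The control group will be given conventional perioperative medications according to guidelines of atrial fibrillation". No placebo or active comparator is given. The trial group receives the same conventional therapy plus sacubitril/valsartan.
- **Background medication.** Under Conventional perioperative medications, for all patients: "They will be on an uninterrupted anticoagulation regimen during the perioperative period".
- **Blinding.** "This trial is designed as an open label"; participants and care givers know the allocation.
- **Start of the trial drug.** For patients taking an ACEI, "they will be given the trial drug starting 36 h after discontinuation of ACEI drugs".

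**The concern.** Intention to treat means that everyone randomised is analysed in the arm to which they were allocated. A set that also requires a first dose depends on something that happens after randomisation. Here the arm is already known when that happens, and only one arm has a new drug to start. If patients drop out of the set because they did not start that drug, their counterparts in the control arm cannot be identified and stay in. The two analysed groups may then differ in prognosis for reasons other than treatment.

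The eligibility condition raises a related but separate question. If applied after randomisation, it would allow patients in either arm to be removed.

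The primary comparison of sinus rhythm maintenance and the MACE comparison are at stake. So is the article's statement that overall type I error is held at 0.05, because that assumes the analysed groups are the randomised groups. While the drugs stay undefined, the choice of population also remains open to interpretation when the data are in.

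**Working it through.** **1. What the dose condition does under each reading**

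| Drugs means | Sacubitril/valsartan arm | Control arm |
|---|---|---|
| Sacubitril/valsartan only | non-starters removed | every patient removed |
| The allocated treatment | non-starters removed | almost nobody removed |
| Any drug, background included | almost nobody removed | almost nobody removed |

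The first reading cannot be intended. The third makes the condition idle. Only the second gives a working rule, and under it the loss falls almost wholly on one arm.

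**2. Inputs for the size of a bias**

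- From the Sample size section: 42% recurrence at 12 months, 231 patients per arm, one-sided 0.05.
- Not in the article, so assumed: the share x of the active arm that never starts (2%, 5%, 10%) and the recurrence risk q of those patients (42%, 60%, 80%).

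**3. Shift in the active-arm rate with no drug effect**

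Analysed rate = (0.42 − x·q)/(1 − x). The fall from 42% is x(q − 0.42)/(1 − x).

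- x = 0.05, q = 0.60: (0.42 − 0.030)/0.95 = 0.4105, a fall of 0.9 points.
- x = 0.10, q = 0.60: (0.42 − 0.060)/0.90 = 0.400, a fall of 2.0 points.
- q = 0.42: no shift, whatever x is.
- q below 0.42: the shift reverses and works against the drug. For example, with x = 0.10 and q = 0.24, (0.42 − 0.024)/0.90 = 0.440.

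**4. Effect on type I error**

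With whole patients removed from 231 and a normal approximation at a single look:

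error = 1 − Φ(1.645 − δ/SE), where δ = 0.42 − p, SE = √[0.42·0.58/231 + p(1 − p)/(231 − m)], m is the number removed and p is the analysed rate.

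| Removed | Their risk | Analysed rate | One-sided error (nominal 0.050) |
|---|---|---|---|
| any | 42% | 42.0% | 0.050 |
| 5 (2%) | 60% | 41.6% | 0.060 |
| 5 (2%) | 80% | 41.2% | 0.072 |
| 12 (5%) | 60% | 41.0% | 0.076 |
| 12 (5%) | 80% | 39.9% | 0.116 |
| 23 (10%) | 60% | 40.0% | 0.111 |
| 23 (10%) | 80% | 37.8% | 0.228 |

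Twelve of 231 is 5.2%, so that row shows 41.0% where exactly 5% gives 41.1%.

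**5. Cost of analysing all randomised patients**

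The stated ratio of 0.46 fits an absolute fall from 42% to 22%: ln(0.78)/ln(0.58) = 0.456. If 10% of the active arm never start and carry the control risk, the arm's rate is 0.9·0.22 + 0.1·0.42 = 0.24.

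Two-proportion power is Φ[(0.42 − p_T − 1.645·SE₀)/SE₁], with SE₀ = √[2p̄(1 − p̄)/n] and SE₁ = √{[0.42·0.58 + p_T(1 − p_T)]/n}.

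- n = 231: for p_T = 0.22, Φ[(0.200 − 0.0714)/0.0424] = 99.9%. For p_T = 0.24, Φ[(0.180 − 0.0720)/0.0429] = 99.4%.
- n = 185 (231 less 20%): for p_T = 0.22, Φ[(0.200 − 0.0798)/0.0474] = 99.4%. For p_T = 0.24, Φ[(0.180 − 0.0804)/0.0480] = 98.1%.

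**The case against.** The strongest reply is that the article does not say *trial drug* here, although the Interventions section uses that term for sacubitril/valsartan. Both arms receive conventional medication, so if that counts, the condition removes almost nobody and no bias follows. This stands. A one-sided loss is conditional on reading the drugs as the allocated treatment.

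Three stronger inferences are tempting, and the article does not support them.

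- **That eligibility will be re-checked, mainly to one arm's cost.** The Randomization and allocation section describes patients who meet the criteria being enrolled and then randomised. The population sentence may only repeat that sequence. No later review is described, and one would touch both arms. What remains is that the wording does not rule out exclusion after randomisation.
- **That many active-arm patients will not start.** The article has safeguards. Patients with low mean postoperative blood pressure are excluded. Participants have 24 hours to consider and must agree to all study steps. The investigator may exclude those judged unable to follow the protocol. The ACEI interval is not said to begin after randomisation, nor is anyone said to be lost during it. These points reduce non-starting but do not exclude it.
- **That the definition favours the drug, or that randomisation no longer protects the comparison.** Nothing in the article gives the recurrence risk of non-starters. At average risk the bias is nil, and below it the direction reverses.

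It is also fair to say that 1–2 points is small beside the planned 20-point difference, and that a fuller protocol or analysis plan may hold more. But the article chose to define the population, and what it states conflicts with the principle one sentence earlier.

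**Conclusion.** The point holds as an inconsistency in the stated analysis population. The article promises intention to treat, defines a modified ITT set under that name, leaves the qualifying drugs undefined, and states no analysis of all randomised patients. This does not depend on any assumption.

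The consequence is conditional. If the drugs are the allocated treatment, the dose condition can remove patients almost only from the sacubitril/valsartan arm. With an assumed 5–10% of non-starters at an assumed 60% recurrence, the active-arm rate would look about 1 to 2 points better with no drug effect, and one-sided type I error would be about 0.076 to 0.111 instead of 0.050. These error figures come from a single-look approximation for two proportions, not from the planned log-rank test with interim looks. The bias is zero if non-starters carry the average risk, or if background medication satisfies the condition. A reader should not conclude that the trial is biased towards the drug, only that the definition leaves room for a bias of unknown size and direction that can be closed at almost no cost.

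**What to change.** Replace the population sentence with a definition of ITT as all randomised patients, analysed in their allocated arm regardless of dosing or of ineligibility found later. State that the primary and MACE analyses use it. Keep the dosed set only as a labelled modified-ITT sensitivity population or safety population, and say there which drugs count towards the dose condition in each arm.

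The change takes a sentence or two. The article describes the trial as still recruiting, so it can be made by amendment before the final outcome comparison. The downside is slight dilution from patients who never start: under the plan's own 42% against 22%, even 10% non-starters at control risk leave power at 98.1% with 185 per arm.
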